**Discussion:**

Two modifications to the traditional LP technique (sitting vs lying position; and early vs late stylet removal) will be simultaneously investigated in an efficient and appropriately-powered 2 × 2 factorial RCT design. Analysis will identify the optimal techniques (in terms of obtaining easily-interpretable cerebrospinal fluid), as well as the impact on infants, parents and healthcare systems whilst providing robust safety data. Using a pragmatic RCT design, all practitioners will be trained in all LP techniques, but there will inevitably be variation between unit practice guidelines and other aspects of individual care.

An improved LP technique would result in:

• Fewer uninterpretable samples, repeated attempts and procedures

• Reduced distress for infants and families

• Decreased antibiotic use and risk of antibiotic resistance

• Reduced healthcare costs due to fewer procedures, reduced length of stay, shorter antibiotic courses, and minimised antibiotic-associated complications

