## Background

Neonatal bacterial meningitis has high rates of mortality and morbidity in Europe and North America, and higher still in Africa and Asia [1]. The symptoms and signs are non-specific in neonates, and the diagnosis can only be confirmed by analysing cerebrospinal fluid (CSF), following lumbar puncture (LP). Infants with meningitis typically require 14–21 days of inpatient intravenous antibiotics, incurring significant financial costs, and often receive hospital follow-up due to the risk of long-term neurological sequelae [2]. Prolonged antibiotic use is associated with significant complications [3, 4]. If meningitis can be excluded, antibiotics are usually stopped after 5 days, allowing discharge with no further follow-up.

Each year up to 30,000 UK newborn infants undergo LP [5], but success rates are much lower in neonates (50–60%) [6, 7] than older children (78–87%) [8, 9]. Interpretation of non-clear CSF samples containing significant numbers of red blood cells (RBC) (> 5000, or > 10,000 RBC/mm^3^) is challenging and the presence/absence of meningitis difficult to confirm. Thus, LPs often need repeating, and lead to treatment with extended courses of antibiotics because meningitis cannot be excluded.

LP techniques currently vary by local practice. Several modifications to ‘traditional’ technique have been investigated, but few have good evidence of benefit. Two modifications identified during a literature review appeared the most promising and amenable to investigation in an RCT:
Sitting position, in which the infant is held in a semi-upright, sitting position compared to lying (‘lateral decubitus’) position.‘Early stylet removal’ (ESR), which is the removal of the stylet from the LP needle shaft once it has penetrated the subcutaneous tissue, and before advancing the needle into the CSF.

Sitting: the only published systematic review regarding LP in children/neonates examined sitting position and concluded that “Positions other than the lateral decubitus may be equal or superior in terms of lumbar puncture success” …and… “A large-scale prospective clinical trial directly addressing LP success and safety in different positions would clarify the need to change current practice” [10].

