### Statistics and analysis

#### Sample size and power calculation

Four hundred eighty-three infants are required for each arm of the main comparison (sitting vs lying position and ESR vs LSR), to detect a 10% absolute difference (from 59 to 69%) in the proportion of infants with successful LPs, with 90% power, a 5% two-sided significance level and assuming (based on expert opinion and the lack of external evidence) no interaction effect between infant position and timing of stylet removal. Allowing for 5% attrition, the required recruitment target is 1020 (255 in each of the four groups). The 59% control event rate was derived from local prospective cohort data [30] and corroborated by published UK data [20]. We estimate 50% parental uptake rate and minimal ‘loss to follow-up’ as all data will be collected pre-discharge.

Modelling suggests we will need 10 local Neonatal Units and Neonatal Intensive Care Units to recruit enough infants within 24 months, with a recruitment rate of around 5 infants per centre per month assuming: staggered starts (two centres per month), and each centre taking 4 months to reach stable recruitment rate. PMG will implement recruitment initiatives and additional centres, based on actual recruitment.

Our inclusion/exclusion criteria are designed to minimise protocol deviations by only including infants who can be sat up. Only sparse safety data is available for LPs < 27 weeks and < 1000 g; hence these infants will be excluded from our trial.

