#### Description of statistical methods

Outcomes for participants will be analysed in the groups to which they are assigned regardless of deviation from the protocol or allocation received, but will be excluded from the analysis if no LP procedure was received (modified intention-to-treat analysis). To assess the effect of position we will compare groups (1–Lying/LSR) plus (2–Lying/ESR) with groups (3–Sitting/LSR) plus (4–Sitting/ESR), and to assess the effect of the timing of stylet removal we will compare groups (1) plus (3) with groups (2) plus (4). We will calculate the risk ratio (95% Confidence Interval (CI)) for the primary outcome (and all other dichotomous outcomes), the mean difference (95% CI) for normally distributed continuous outcomes or the median difference (95% CI) for skewed continuous outcomes. Absolute risk difference and CIs will also be calculated for tested dichotomous clinical outcomes (to be presented in a supplementary appendix). Groups will be compared using regression analysis, adjusting for the stratification variables used at randomisation. Both crude and adjusted estimates will be presented but the primary inference will be based on the adjusted analyses. Adjusted risk ratios will be estimated using log-binomial regression, or a Poisson regression model with a robust variance estimator in the event of non-convergence. Linear regression will be used for normally distributed outcomes and quantile regression for skewed continuous outcomes.

With a view to minimising the effects of multiple testing given the number of procedures and attempts performed for each infant, and correlation between some outcomes, statistical inference will be restricted to a predefined list of tested outcomes. Summary data by trial arm will be provided for all other outcomes but statistical tests (or the calculation of CIs) will not be performed. A complete list of outcomes that will be tested and not tested statistically are provided in a supplementary appendix.

Full details of the statistical analysis will be documented in the Statistical Analysis Plan.

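### A median difference is a poor between-arm estimate for antibiotic duration: on the protocol's figures most infants in both arms are expected to have the short course, so a real benefit can show as zero

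*Protocol article*

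**What the plan says.** Protocol article, *Description of statistical methods*: continuous outcomes get a mean difference if normally distributed and a median difference if skewed, each with a 95% CI. The models follow from that: "Linear regression will be used for normally distributed outcomes and quantile regression for skewed continuous outcomes". Primary inference is on estimates adjusted for the stratification factors. Tests and CIs are limited to a predefined list of outcomes held in a supplementary appendix, and full details are left to the SAP. Neither is shown.

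*Outcomes related to cost and safety* lists the duration of the antibiotic course. On its distribution, *Background* says: "If meningitis can be excluded, antibiotics are usually stopped after 5 days, allowing discharge with no further follow-up". It gives 14–21 days for infants with meningitis and says that uninterpretable samples often lead to repeat procedures and extended courses. It does not give the length of an extended course, the share of failures that receive one, or the share of infants with meningitis.

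*Sample size and power calculation* plans "to detect a 10% absolute difference (from 59 to 69%) in the proportion of infants with successful LPs".

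The Abstract's *Discussion* expects an improved technique to bring "Reduced healthcare costs due to fewer procedures, reduced length of stay, shorter antibiotic courses".

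**The concern.** The technique can shorten antibiotics only by turning a failed first procedure into a successful one. On the planning figures that moves infants out of the upper 31–41% of the distribution. The middle infant in either arm is already in the short-course cluster, so a contrast of medians hardly registers the change. Total antibiotic days, and costs that depend on them, follow the mean.

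At stake is how a secondary outcome central to the trial's rationale would be read. A median difference of 0 invites the conclusion that better sampling does not reduce antibiotic use, even in a trial where it did so to the extent planned.

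**Working it through.** **1. The plan's own figure.** Pooled-variance formula for two proportions, p1 = 0.59, p2 = 0.69, mean 0.64:

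n = [1.960·√(2·0.64·0.36) + 1.282·√(0.59·0.41 + 0.69·0.31)]² / 0.10² = 482.1, rounded up to 483 per side. This reproduces the stated number. 966/0.95 = 1017, rounded up to 1020 as 4 × 255.

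**2. Two-point model of antibiotic duration.** Short course 5 days, long course 14 days. From the article: 59%/69% success, 5 days, 14 days. Assumed: m, the share of infants with meningitis, and f, the share of failures given the long course.

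- Share on the short course: s = (1 − m)·[1 − f·(1 − p)].
- The median of 483 infants is the 242nd ordered value, so it exceeds 5 days with probability P(Bin(483, s) ≤ 241). The median difference is 0 when both arms fall on the same side.
- Mean difference: −9·(s2 − s1). SE = 9·√{[s1(1 − s1) + s2(1 − s2)]/483}. Power = Φ(|difference|/SE − 1.96).

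| m | f | s1, s2 | Median difference = 0 | Mean difference (days) | Power, mean |
|---|---|---|---|---|---|
| 0 | 25% | 0.898, 0.923 | 100% | −0.225 | 27% |
| 0 | 50% | 0.795, 0.845 | 100% | −0.45 | 53% |
| 0 | 100% | 0.59, 0.69 | >99.9% | −0.90 | 90% |
| 5% | 50% | 0.755, 0.803 | 100% | −0.43 | 43% |
| 5% | 100% | 0.56, 0.655 | 99.6% | −0.855 | 86% |
| 10% | 25% | 0.808, 0.830 | 100% | −0.20 | 15% |
| 10% | 50% | 0.716, 0.760 | 100% | −0.405 | 36% |
| 10% | 100% | 0.531, 0.621 | 91% | −0.81 | 81% |
| 15% | 100% | 0.501, 0.586 | 53% | −0.765 | 76% |
| 20% | 25% | 0.718, 0.738 | 100% | −0.18 | 10% |

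With a 21-day long course the mean differences scale by 16/9 (−0.90 becomes −1.6) and the power is the same. When f = 100%, the control median leaves 5 days once m passes 1 − 0.5/0.59 = 15%. Near that point the estimate flips between 0 and −9 days.

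**3. Adjustment.** Median regression adjusted for 10 assumed centres and four gestation groups, neither affecting duration (100 simulated trials), gave a coefficient of 0 in 100% of runs with all failures long, with half long, and with all long plus 5% of successes long for meningitis. The adjusted means were −0.96, −0.46 and −0.82 day.

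**4. Without exact ties (no meningitis assumed).**

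- *Continuous spread around 5 days.* The arm median is about 5 + SD·Φ⁻¹(0.5/s). With all failures long, simulated median differences were −0.22, −0.44 and −0.87 day for SD 0.5, 1 and 2 (simulated SE 0.10, 0.20 and 0.40, roughly 58% power). The mean difference was about −0.9 day, with 84–88% power. With half long and SD 1, the medians are 5.33 and 5.23, a difference of −0.10 against −0.45 for the mean.
- *An exception.* With an extended course of only 7 days, continuous spread (SD 1) and all failures extended, the median moved slightly more than the mean (−0.25 against −0.20).
- *Whole days.* With half of failures long and SD 1, the adjusted coefficient was 0 in 99% of runs. With all failures long, the crude difference was 0 in 44%, 84%, 43% and 9% of runs for SD 0.5, 1, 1.5 and 2. The figure swings because a median near a half-day boundary rounds either way, so the estimate jumps by a whole day.

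**The case against.** The strongest objection is that the article does not establish the distribution. It says only that antibiotics usually stop after 5 days, and everything about spread, extended courses and meningitis frequency is assumed. That stands. A reader might infer that the median difference will be about zero whatever happens. Step 4 and the 15% row show otherwise: the median can shift, or jump.

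Second, inference is restricted to a list that is not shown. If antibiotic duration is not on it, no median difference with CI will be reported. That also stands, and it makes the point conditional.

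Third, a reader might infer that quantile regression is fixed for every skewed outcome, including the number of procedures and attempts. The text does not support this. It says skewed continuous outcomes, these are counts, and the article assigns counts no method, which may properly be left to the SAP. If they were handled as skewed outcomes, both medians of procedures would be 1, but that is a hypothetical. Nor is there a basis for extending the point to length of stay, since nothing shows that its median is tied.

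Fourth, the mean is not a strong test either: about 10–53% power in the rows where at most half of failures lead to long courses. True, but an imprecise estimate of the quantity that changes is more useful than an exact zero for one that does not.

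Deferring details to the SAP does not answer the point, because the effect measure for skewed continuous outcomes is stated in the article.

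**Conclusion.** The concern holds for antibiotic duration, conditionally. On the protocol's success rates and its account of treatment, more than half of each arm is expected in the short-course cluster. Given heavy ties at 5 days, a long course for only some failures and uncommon meningitis, the median difference is 0 in nearly all trials while the mean falls by about 0.2–0.9 day. In the two-point model with 0–10% meningitis the zero appears in about 91–100% of trials, even if every failure gets the long course. With continuous spread the median moves, usually by less than the mean and with less power. If nearly all failures lead to long courses, it can be unstable, by a day or more.

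This affects the interpretation of one secondary outcome. It does not touch the primary outcome or the sample size.

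**What to change.** In the SAP, if antibiotic duration is on the list of tested outcomes, make its between-arm estimate the difference in arithmetic means, adjusted for the stratification factors, with a robust or bootstrap 95% CI. Keep median (IQR) by arm as description. The general rule for other skewed continuous outcomes can stay, and no change is proposed for length of stay.

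The cost is one short paragraph and no new data. The downside is that the mean is more sensitive to a few very long courses, which the CI and the IQR will make visible. Power stays modest, about 10–50%, unless most failures lead to long courses, so the result should be read as an estimate with its interval.

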#### Interaction testing

The interaction between sitting/lying position and the timing of stylet removal will be investigated for the primary outcome, though we acknowledge that the trial is not powered to detect an interaction effect. A descriptive multi-arm analysis will also be presented for the primary outcome, other tested outcomes, and baseline characteristics (i.e. for each of the four trial arms) as supplementary information [31].

#### Interim data monitoring

Interim data monitoring will be carried out by the DMC at least annually. The DMC Charter will include details about timings of reviews, contents of the reports and any stopping guidelines.

## Discussion

### Participant risks and benefits

All trial participants will be having an LP as part of routine clinical care. All techniques are in current use and none is proven to be more or less safe than another. No infants are expected to be placed at risk as a result of being in the trial. Serious complications of LP are rare. Some complications can be prevented by avoiding LPs in infants with contraindications such as coagulopathy; or mitigated, e.g. with sterile technique. Potential benefits of trial participation include: an optimised analgesia protocol; all infants will have heart rate and oxygen saturations monitored during the procedure.

### Parent questionnaire

Parents completing the STAI-S questionnaire will be asked about their feelings and levels of anxiety which are sensitive and upsetting topics. Our PPI group and previous research has indicated that in stressful situations, parents benefit from being given the opportunity to express their feelings. Completion of the questionnaire will not be pursued if a parent becomes distressed when completing it.

### Consent

Ideally, consent will be given at such time to allow randomisation and enable the clinical team to prepare for that procedure. However, in instances where this is not possible, the LP will not be delayed if, in the opinion of the infant’s clinician, any delay would be deemed clinically unsound: in such cases, the infant would not be recruited to the trial.

### Participant confidentiality

The infants’ and parents’ names will be shared with NPEU CTU via the consent form. Parents of infants participating in the trial will be informed of, and provide consent to this. No other personal identifiable information will be shared outside of the site.

Overall responsibility for ensuring that each participant’s information is kept confidential lies with the Sponsor. All paper documents will be stored securely and kept in strict confidence in compliance with current data regulations. Data collected on the (e)CRFs will be stored in an electronic database held by the Trial Coordinating Centre in which the participant will be identified only by a trial specific number.

Following trial completion and report publication, data will be archived in a secure physical and electronic location with restricted access.

### Participant remuneration

No financial or material incentive or compensation will be provided to parents for enrolling their infants in this trial.

### Dissemination

The success of the trial depends on a large number of research nurses, neonatal nurses, doctors, and parents. Credit for the trial findings will be given to all who have collaborated and participated in the trial including all local coordinators and collaborators, members of the trial committees, the NeoCLEAR Coordinating Centre and trial staff. Authorship at the head of the primary results paper will take the form “[name], [name] and [name] on behalf of the ‘The NeoCLEAR Collaborative Group’”. All contributors to the trial will be listed at the end of the main paper, with their contribution identified. It is the intention of the NeoCLEAR Collaborative Group to present data at national/international conferences and to publish open-access, peer-reviewed articles, including the analysis of key outcomes. The NPEU Clinical Trials Unit and local newborn charity will disseminate the results at conferences and coordinate press releases, website promotion, social and other media interest.

## Data Availability

Not applicable.

## Abbreviations

CGA: Corrected gestational age
CSF: Cerebrospinal fluid
CTU: Clinical Trials Unit
DMC: Data Monitoring Committee
eCRFs: Electronic Case Report Forms
ESR: Early stylet removal
HRA: Health Research Authority
LP: Lumbar puncture
LSR: Late stylet removal
NIHR: National Institute for Health Research
NPEU: National Perinatal Epidemiology Unit
PCR: Polymerase Chain Reaction
PMNs: Polymorphonuclear Leukocytes
PPI: Patient and public involvement
RBC: Red Blood Cell(s)
RCT: Randomised controlled trial
REC: Research Ethics Committee
SAE: Serious Adverse Event
SSNAP: Support for the sick newborn and their parents
STAI-S: State-Trait Anxiety Inventory Subscale
TSC: Trial Steering Committee
WBC: White Blood Cell(s)
